# Light therapy as a treatment of cancer-related fatigue in (non-)Hodgkin lymphoma survivors (SPARKLE trial): study protocol of a multicenter randomized controlled trial

**DOI:** 10.1186/s12885-018-4746-2

**Published:** 2018-09-10

**Keywords:** Cancer related fatigue, Light therapy, Sleep quality, Randomized controlled trial, Hematology, Circadian rhythms

## Abstract

**Background:**

Cancer related fatigue (CRF) is one of the most prevalent and distressing long-term complaints reported by (non-) Hodgkin survivors. To date there has been no standard treatment for CRF in this population. A novel and promising approach to treat CRF is exposure to bright white light therapy. Yet, large scale randomized controlled trials testing its efficacy in these patients and research on potential mechanisms is lacking. The objective of the current study is to investigate the efficacy of light therapy as a treatment for CRF and to explore potential mechanisms.

**Methods/design:**

In a multicenter, randomized controlled trial we are evaluating the efficacy of two intensities of light therapy in reducing CRF complaints and restrictions caused by CRF in survivors of Hodgkin lymphoma or diffuse large B-cell lymphoma. Secondary outcomes include sleep quality, depression, anxiety, quality of life, cognitive complaints, cancer worries, fatigue catastrophizing, self-efficacy to handle fatigue, biological circadian rhythms of melatonin, cortisol and activity, and biomarkers of inflammation. We will recruit 128 survivors, with fatigue complaints, from academic and general hospitals. Survivors are randomized to either an intervention (exposure to bright white light) or a comparison group (exposure to dim white light). The longitudinal design includes four measurement points at baseline (T0), post-intervention at 3.5 weeks (T1), 3 months post-intervention (T2) and 9 months post-intervention (T3). Each measurement point includes self-reported questionnaires and actigraphy (10 days). T0 and T1 measurements also include collection of blood and saliva samples.

**Discussion:**

Light therapy has the potential to be an effective treatment for CRF in cancer survivors. This study will provide insights on its efficacy and potential mechanisms. If proven to be effective, light therapy will provide an easy to deliver, low-cost and low-burden intervention, introducing a new era in the treatment of CRF.

**Trial registration:**

The study is registered at ClinicalTrials.gov on August 8th 2017(NCT03242902).

## Background

After the introduction of modern radiotherapy and combination chemotherapy, Hodgkin lymphoma (HL) has become the prototype of a curable malignancy with cure rates of 80 to 90% [1]. Also, for selected patients with aggressive non-Hodgkin lymphoma, survival has improved significantly, i.e. the 5-year overall survival of patients with diffuse large B-cell lymphoma (DLBCL) varies from 40 to 85% [2]. Unfortunately, treatment of lymphoma is associated with various late adverse effects, including cancer related fatigue (CRF) [3].

CRF is defined as “a distressing, persistent, subjective sense of physical, emotional, and/or cognitive tiredness or exhaustion related to cancer and/or cancer treatment that is not proportional to recent activity and interferes with usual functioning” [4, 5]. Patients feel tired even after resting, have reduced capacity to carry out normal activities, experience slow physical recovery from tasks, and report diminished concentration [6]. CRF is one of the most frequently reported long-term symptoms in (non-) Hodgkin survivors with prevalence ratings between 25 to 60% compared to 10 to 25% in the general population [7, 8]. CRF significantly affects patients’ quality of life [5] and seems to be influenced by symptoms of depression, anxiety, and the presence of comorbid conditions [8].

Currently, there is no standard treatment for CRF. A range of non-pharmacological interventions to treat CRF have been investigated, including physical activity (PA), psycho-education, cognitive-behavior therapy (CBT), CBT with hypnosis (CBTH), mindfulness-based approaches, and a number of complementary and alternative medicine interventions (e.g., acupuncture/acupressure, yoga, music therapy) [5]. Some of these interventions, including PA [9, 10], CBT [11], and CBTH [12], have been associated with large effect sizes. In the case of CBT, these effects remain stable for at least 2 years [13]. These findings are promising but not without limitations. For example, motivation is essential to complete these interventions while fatigue can reduce the motivation for PA [14]. Also, CBT is labor intensive since it requires professional guidance for several weeks.

A new development in the treatment of CRF is the use of light therapy. During this therapy, patients are asked to expose themselves to bright white light (BWL) for 30 min within the first half hour after awakening. Systematic exposure to BWL was originally developed to treat seasonal affective disorder [15] and is currently the treatment of choice for this disorder [16–18] although a recent review provided less conclusive results [19]. Additionally, light therapy has been found to help restore circadian rhythm disturbances and sleep disorders [20, 21].

Several studies have investigated the efficacy of light therapy specifically for CRF. One study randomized breast cancer patients undergoing chemotherapy to either a BWL (*n* = 23) or a dim red light (DRL; *n* = 16) condition [22]. Results showed that the usual increase in CRF from baseline to the end of the fourth chemotherapy cycle was seen in women exposed to DRL, while such an increase was not seen in the group exposed to BWL. In addition, circadian rhythms became more synchronized and quality of life was better in the women exposed to BWL compared to women exposed to DRL. Another study used the same design to test the efficacy of light therapy for CRF in cancer survivors [23]. Results showed that fatigue decreased to normal levels in survivors exposed to BWL (*n* = 18) while survivors exposed to DRL (n = 18) stayed at clinically significant levels of fatigue. These results also showed a significant decrease in depressive symptoms and better sleep quality in survivors exposed to BWL compared to DRL. More recently, results were published from a larger RCT that included 81 cancer survivors [24]. Survivors exposed to BWL showed greater reductions in fatigue and improvements in mood, depressive symptoms and quality of life compared to survivors exposed to DRL. In summary, these findings support the use of light therapy as a treatment for CRF.

However, the mechanisms that explain the effect of light therapy on CRF have largely remained unexplored. Light is one of the strongest synchronizers of the circadian rhythm system [25]. When it enters the eye, light affects processes in the suprachiasmatic nucleus (SCN), a structure better known as the human master pacemaker of circadian rhythms [26]. Based on this knowledge, several hypotheses about potential mechanisms could be formulated.

The first hypothesis is that light therapy normalizes the sleep-wake cycle. Previous studies showed that sleep-wake cycles, measured with questionnaires as well as objective measurements with actigraphy, were disrupted in patients with cancer after chemotherapy and that this disruption was related to increased CRF [22, 27]. Furthermore, it was shown that light therapy during chemotherapy resulted in sleep-wake cycles that returned to baseline levels after chemotherapy while patients in the comparison condition showed disrupted sleep-wake cycles after four cycles of chemotherapy [27]. Moreover, secondary analysis on objective sleep data collected with actigraphy in cancer survivors with CRF suggested that exposure to bright white light improved the sleep efficiency to normal ranges while this improvement was not seen in the group exposed to dim red light [28].

The second hypothesis is that the mechanism may be related to changes in circadian rhythms. The superchiasmatic nucleus (SCN) is responsible for the production of melatonin, a hormone that is secreted in darkness, which acts as a time-cue for sleep. Melatonin shows a circadian rhythm with rising levels during the evening that reaches the peak during the night followed by a decrease that reaches its lowest point (nadir) in the morning. The SCN also plays a role in the production of cortisol, a glucocorticoid hormone that shows a sharp increase in the first 30 min after awakening, followed by a gradual decline over the day that reaches its nadir during the night [29]. Impairments of this rhythmicity, such as the flattened morning-rise and a lower ratio between morning and nocturnal levels of cortisol, have consistently been associated with deteriorations in mood in both healthy and clinical populations and increased CRF in clinical populations [30–32]. Light therapy was proven to be effective in entrainment of the circadian rhythms of melatonin and cortisol [33]. Moreover, improvements in CRF over time were associated with normalization of the circadian cortisol rhythm [34], suggesting that a potential mechanism of light therapy on CRF is via the normalization of the circadian rhythms of these hormones.

A third potential mechanism is the normalizing effect of light therapy on the HPA axis, which may affect inflammatory cytokine activity. There is a wealth of research, both in animals as well as in clinical and healthy human populations, showing strong interconnections between fatigue and inflammation. Consistent associations have been shown between CRF and plasma levels of inflammatory markers such as interleukin-6 and C-reactive protein [35, 36]. There is also a well characterized feedback loop between the HPA axis and inflammation, whereby the HPA axis can down regulate inflammation and is itself up regulated by inflammatory signaling [37]. BWL has been found to normalize HPA axis function [38] raising the possibility that BWL may affect inflammatory cytokine activity either directly or indirectly, e.g., via its normalizing effects on the HPA axis.

The main aim of this double-blind, randomized controlled trial, called ‘improving Sleep quality, Psychosocial functioning and cAncer Related fatigue with Light thErapy (SPARKLE)’, is to determine the effect of exposure to BWL compared to exposure to dim white light (DWL), on CRF in ≥2 years survivors of HL and DLBCL. Additionally, this trial will explore potential mechanisms of light therapy on CRF by investigating the influence of light therapy on factors associated with CRF. More specific, the secondary objectives are:to examine the effect of exposure to BWL compared to DWL on sleep quality and psychological variables (depression, anxiety, cognitive complaints, and quality of life).to investigate whether exposure to BWL, compared to DWL, affects circadian rhythms of cortisol and melatonin, activity, vitamin D concentrations and levels of biomarkers for inflammation markers.to explore whether the effects of exposure to BWL on CRF can be predicted by the effect of BWL on sleep quality, psychological variables, biological and activity circadian rhythms, and inflammation markers.

## Methods

This trial will use a double blind randomized controlled trial design with one intervention group exposed to bright white light and one comparison group exposed to dim white light. The design of the trial and the anticipated flow is shown in Fig. 1. This trial (under number NL61017.031.17) has been approved by The Institutional Review Board of The Netherlands Cancer Institute as well as by the review boards of the participating hospitals (see recruitment and randomization). Patient recruitment and data collection started in August 2017.

**Fig. 1 Fig1:**
[figure not shown]
Overview of the trial design

### Participants

The intended study sample will comprise 128 survivors of Hodgkin lymphoma (HL) or diffuse large B-cell lymphoma (DLBCL). Inclusion criteria are: (1) a survivorship of ≥2 years; (2) presence of moderate to severe fatigue symptoms since diagnosis of or treatment for HL or DLBCL. The presence of fatigue will be defined by fulfilling at least one of the following criteria: (a) a moderate to severe fatigue score on the general fatigue subscale of the multidimensional fatigue index; (b) a score of ≥17 on the Work and Social Adjustment Scale indicating clinical levels of impairments in daily functioning caused by fatigue [39].

Exclusion criteria are: (1) presence of somatic cause for fatigue (defined as (a) New York Heart Association class 3/4 (heart failure), (b) having a COPD gold class 3/4 (lung failure), or (c) having other organ failure that has led to marked limitation of physical activity). Patient can be included if, despite having used stable medication for ≥6 months for the somatic cause, fatigue complaints remain; (2) pregnancy (until 3 months postnatal) or lactating; (3) having had extensive surgery in the past 3 months; (4) having a current diagnosis of psychiatric disorder that can hamper participation; (5) having had a diagnosis of and/or treatment for secondary malignancy in the past 12 months; (6) presence of photophobia or other eye diseases that show symptoms of photophobia; (7) current or previous use of light therapy (≥ 1 week); (8) current employment in shift work.

### Recruitment

Participants for this study will be recruited via collaborating BETER-clinics. The BETER consortium (Better care after Hodgkin lymphoma: Evaluation of long-Term Treatment Effects and screening) is organising a nationwide infrastructure for survivorship care for lymphoma survivors, to prevent morbidity and mortality from late treatment effects [40]. This consortium identifies and traces 5-year survivors of HL and DLBCL treated in 23 Dutch academic as well as general hospitals. So far, eight BETER-clinics agreed to collaborate with the SPARKLE study: Antoni van Leeuwenhoek, LUMC, Radboudumc, VUmc, UMCU, ErasmusMC, Albert Schweitzer hospital, HagaZiekenhuis, Admiraal de Ruyter hospital.

Survivors (≥ 2 years) of HL or DLBCL who visit their treating physician for follow-up care are screened for CRF symptoms. When CRF symptoms are present and the patient meets the inclusion criteria, the physician will hand out a pamphlet, a response card and a screening questionnaire to the patient. A second strategy to recruit patients is via an evaluation of the BETER screening questionnaire that patients complete for their first BETER-clinic visit. This questionnaire includes a visual analogue scale (VAS) scale from 0 (no fatigue) to 10 (worst imaginable fatigue). If the fatigue score is 4 or higher, patients will be sent the information package.

Patients are asked to return the response card to express their interest in participation. In case of no interest, patients are asked to specify their reason(s) on the response card. If patients are interested, they are asked to complete the screening questionnaire and return this to the SPARKLE research team. Non-responders will receive a reminder 3 weeks after receiving the information package.

Patients who return the screening questionnaire receive a call from the SPARKLE research team. The aim of this phone call is to provide more information about the study and to screen on inclusion and exclusion criteria. Interested and eligible patients will receive a more detailed patient information letter and an informed consent form. Patients are requested to return a signed informed consent or a no-interest-response-card within 2 weeks. Non-responders will be called to assess willingness for participation 3 weeks after sending the patient information letter.

### Randomization

Equally distributed across all four seasons, participants are randomized to either an intervention group (*n* = 64) or a comparison condition (*n* = 64) using the minimization technique at a 1:1 ratio. Randomization is stratified for diagnosis (HL; DLBCL), time since diagnosis (< 5 years; 5–10 years; 11–20 years; > 20 years) and gender (male; female). Randomization is outsourced to an independent party, using the randomization programme ALEA. The output determines which lamp (with BWL or with DWL) is offered to each participant. This lamp will be part of the content of a bag offered to the research assistant who visits the participants. In this way, both the research team and the participants are blinded to the allocated condition. The randomization code will only be broken if a patient reports severe adverse side effects as a result of the light intervention.

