### Study measures

#### Sociodemographic and clinical data

Information regarding the patients’ age, education, marital status, living situation, work status and medication use will be obtained via a questionnaire. Clinical information, including date of diagnosis, tumor characteristics, and treatment history will be abstracted from the BETER-database. This clinical information will be abstracted from the patients’ medical record when participants are not included in the BETER-consortium. Current season will be derived from the start date of light therapy.

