#### Statistical analyses

Data will be analysed using the Statistical Package for the Social Sciences (SPSS). Although we endeavour to check all questionnaires upon their return and call participants to complete missing items, some data might still be missing. Missing values will be imputed according to the manual of the questionnaire. In general, descriptive statistics will be computed for the outcome variables, potential covariates and demographic variables. Bivariate analyses will be undertaken to explore associations between outcome and potentially confounding variables (e.g. season, diagnosis, years since diagnosis) using correlations (for continuous variables) and Chi-square tests (for categorical variables).

Group differences in change in fatigue during the trial will be investigated using a mixed effect growth model with random intercept and slope, nested within site (clusters of different hospitals). This approach takes into account the within and between person variability, and deals adequately with missing data [66]. If baseline differences are identified despite randomisation, these variables will be accounted for in the model. In case of non-ignorable dropout we will correct the model for different patterns of missing values [67]. All analyses will be done on an ´intention to treat´ basis. Additional explorative analyses will be done on a ´per protocol´ basis.

The mixed effect model approach described for change in fatigue will also be used to determine treatment effects of continuous secondary outcome measures. To evaluate between-group differences in categorical secondary outcome measures, we will use generalized estimating equations (GEE) for longitudinal data. This approach accounts for correlated within subject responses, allows for not normally distributed variables and deals adequately with missing data [67–69]. Since there are multiple outcomes, the *p*-values for each model will be adjusted for multiple comparisons.

Within the intervention group we will explore which variables are predictive for the efficacy of light therapy in reducing fatigue. A mixed effect model for longitudinal data will be used with fatigue as dependent variable and the following independent variables: sleep quality, depression, anxiety, cognitive complaints, quality of life, and biological circadian rhythms. The *p*-values will be adjusted for multiple testing.

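### Season and the minimisation factors reach the fatigue model only through a data-driven screen; they should be prespecified covariates, and the seasonal-distribution phrase should be explained

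*Protocol article*

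**What the plan says.** Four places in the protocol article bear on this.

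- **Randomization.** The section opens with "Equally distributed across all four seasons" and allocates 64 participants to each arm "using the minimization technique at a 1:1 ratio". The factors follow: "Randomization is stratified for diagnosis (HL; DLBCL), time since diagnosis" in four bands, "and gender (male; female"). Season is not listed, and the Recruitment section gives no seasonal quota or pacing rule.
- **Sociodemographic and clinical data.** "Current season will be derived from the start date of light therapy", so each participant has one value.
- **Statistical analyses, covariates.** Bivariate analyses explore how outcomes relate to "potentially confounding variables (e.g. season, diagnosis, years since diagnosis"), using correlations for continuous variables and "Chi-square tests (for categorical variables"). Then: "If baseline differences are identified despite randomisation, these variables will be accounted for in the model".
- **Study procedure.** T1 directly follows 3.5 weeks of light therapy; T2 and T3 come 3 and 9 months after it.

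**The concern.** The treatment is light, and the article itself puts season first among its examples of possible confounders. Yet it states a seasonal distribution without a mechanism, and it makes season's place in the model depend on the data.

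The same rule governs the minimisation factors. Minimisation makes the arms alike on diagnosis, time since diagnosis and gender, so these will seldom show a baseline difference and will seldom be adjusted for. If they predict fatigue, leaving them out gives standard errors that are too large for the design used, because the analysis ignores balance that the allocation has forced. Choosing covariates after looking at the data also leaves the primary model open until then.

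At stake are some precision, standard errors that match the allocation, and a primary analysis fixed in advance. The validity of the trial is not at stake.

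**Working it through.** **1. The plan's own figure.** Inputs from Sample size calculation: effect 0.5 SD, alpha 0.05, power 80%, 64 per group. A two-sided two-sample t-test needs 63.8, so 64, per arm; power at 64 is 0.801. The 128 is reproduced, and nothing below changes it.

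**2. The named tests against the variables.** Season has four categories. The primary outcomes (MFI, VAS, WSAS) are scores. A correlation needs two ordered or continuous variables, and a chi-square test needs two categorical ones. Neither fits season against a fatigue score. Chi-square would fit season against a categorical secondary outcome.

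**3. Season at follow-up.** Taking 3.5 weeks as 25 days, I counted every start date in a year, added 25 days, then 3 or 9 months. Meteorological and astronomical seasons give the same result:

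| Visit | Start season | One season on | Two on | Three on |
|---|---|---|---|---|
| T1 | 73% | 27% | 0% | 0% |
| T2 | 0% | 73% | 27% | 0% |
| T3 | 27% | 0% | 0% | 73% |

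The 27% is about 25/91.25, the chance that the treatment period crosses a season boundary.

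**4. Arm imbalance within season.** Simulation of 128 participants, 2,000 runs per setting. Assumptions not in the article: uniform accrual over 2 years, 30% DLBCL, 50% female, and 15/30/30/25% in the four time-since-diagnosis bands. The article does not state the probability of following the minimising allocation, so two values are shown.

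| Allocation | Mean of largest arm difference in any season | Chance of a difference of 6 or more |
|---|---|---|
| Simple randomisation | 8.1 | 80% |
| Listed factors, 80% biased coin | 4.1 | 20% |
| Listed factors, deterministic | 2.5 | 1.3% |
| Season added, 80% biased coin | 2.6 | 2% |
| Season added, deterministic | 1.4 | 0% |

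Minimisation without season already removes much of the imbalance, because allocation runs sequentially through the seasons.

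**5. Translation into bias.** Bias = difference in seasonal share × seasonal effect. With the listed factors and an 80% coin, the 95th percentile of the arm difference in the winter share is 8.5 percentage points. For assumed effects of winter against the rest of the year:

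- 0.3 SD: 0.085 × 0.3 = 0.026 SD
- 0.5 SD: 0.085 × 0.5 = 0.043 SD

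That is about 0.03 to 0.04 SD, or 5% to 9% of the 0.5 SD target, at an unfavourable level of imbalance.

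**6. Precision.** A sinusoidal seasonal swing of amplitude A (in SD) has variance A²/2. For assumed A = 0.2 the share is 0.04/2 = 2%; for A = 0.4 it is 0.16/2 = 8%. If adjustment removed all of it, the standardised effect would rise to 0.5/√0.98 = 0.505 or 0.5/√0.92 = 0.521. Power with 64 per arm would go from 0.801 to 0.809 or 0.833, a gain of about 1 to 3 points.

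**7. Cost of the covariates.** Diagnosis 1, time since diagnosis 3, gender 1, season 3: eight degrees of freedom as main effects in 128 participants. A season-by-time term adds a few more.

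**The case against.** The strongest reply has four parts.

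- **The phrase may mean even accrual.** This stands. The sentence can be read as inclusion spread over the year, and the article does not settle it. A reader might infer that balance between arms within season is promised and then not delivered; the text does not support that as a settled reading. What remains is that the phrase is ambiguous and neither meaning has a stated mechanism.
- **Season can still enter the model.** This also stands. The baseline-difference sentence would admit season if an imbalance were found, so it would be wrong to say that season is only screened. The rule is still data-driven, and it works against the minimisation factors. A separate analysis plan may list covariates, but the article does state a selection rule, and that rule is the point here.
- **Start season is legitimate.** A reader might infer that fixing season at the start is an error. It is not: it is a pre-treatment covariate, and the relevant one for whether season modifies the lamp's effect. Visit timing is the same in both arms, so balance at the start carries forward. Its limit is narrower: as a single main effect it cannot describe seasonal change in fatigue over repeated visits. Nor is T3 always in another season; about 27% of start dates return to their own.
- **The imbalance figures are fragile.** The 20% chance of a difference of 6 or more depends on an assumed 80% coin and falls to 1.3% if allocation is deterministic. It is no evidence of serious bias.

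On chi-square, the description is compressed and exploratory, and the test suits categorical outcomes. The mismatch with the fatigue scores remains, but it does not touch the mixed model itself.

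**Conclusion.** The point holds as a cheap improvement to the analysis. The article states a rule for choosing covariates that depends on the data, names tests that do not fit season against the primary outcomes, and would usually omit the factors used in minimisation. The seasonal phrase in the Randomization section needs its meaning stated.

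A reader might go further and infer that the trial is exposed to material seasonal confounding. The documents and the arithmetic do not support that. Under the assumptions shown, the bias is about 0.03 to 0.04 SD at the 95th percentile of imbalance, the power gain from modelling season is about 1 to 3 points, and the sample size stands. Accrual pattern, coin probability, factor shares and seasonal effect sizes are all assumed. The argument from unfitting tests, and from minimisation factors being left out, needs none of them.

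**What to change.** 1. **Statistical analyses:** stop using the bivariate screen and the baseline-difference rule to choose covariates for the primary model. Prespecify diagnosis, time since diagnosis, gender and season as fixed covariates. The descriptive tables can stay.
2. **Season variable:** derive season at each assessment (T0 to T3) from dates already held and enter it as a time-varying covariate, or keep start season and add a season-by-time term. Say which.
3. **Randomization:** state whether the seasonal phrase means even accrual or balance between arms, and how it is achieved.
4. **Optional:** add season to the minimisation. Recruitment began in August 2017, so this would alter a live allocation system and help only later participants. The covariate is enough without it.

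Items 1 to 3 need no new data, only wording, one derived variable and the degrees of freedom counted above.
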